To compare the incidence of MACE in adults taking statins for primary prevention of CVD between HK, NZ, and the UK; andTo assess the association between LDL-C and non-HDL-C concentrations at 24 months after initiating statin therapy and MACE in adults taking statins for primary prevention of CVD, across three geographically and ethnically diverse populations.

The findings will be relevant to clinicians and organisations developing treatment guidelines worldwide.

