## Method

### Study design

An international, multiple database study will be conducted, using a distributed network approach. Each site will follow a common protocol, to conduct an exposure-based new-user cohort study. The overall study design, study population, criteria for inclusion and exclusion, and follow-up time are shown in Figure 1. The cohort entry date (index date) is defined as the first dispensing or prescribing of a statin between 1 January 2007 and 31 December 2012. To prevent survival bias and covariate measurement bias, a new user, rather than a prevalent user, design will be used. A new statin user is defined as a patient who initiates a statin and received no lipid-modifying therapy prior to the cohort entry date. This protocol is written in accordance with the REporting of studies Conducted using Observational Routinely collected health Data for PharmacoEpidemiology statement (RECORD-PE).^14^

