### Eligibility criteria

To be included in the study, each patient must meet the following eligibility criteria:

Have at least one documented baseline lipid test for total cholesterol (TC), HDL-C, and LDL-C within a year prior to index date.Have at least 12 months of clinical records after registration at the practice site (CPRD) or in the database (PREDICT).Have no previous history of atherosclerotic CVD:defined as a hospital or outpatient diagnosis of coronary heart disease (for example, myocardial infarction, ischaemic heart disease, angina, coronary artery bypass graft, percutaneous intervention), cerebrovascular disease (stroke or transient ischaemic attack), or peripheral artery disease (PAD), prior to index date; ordiagnosis of heart failure, chronic kidney disease, or diabetes with chronic kidney disease, due to their equivalent level of risk as people with established CVD, prior to index date; ora prescribing or dispensing of at least one prescription for nitrates, other antianginal drugs, peripheral vasodilators, loop diuretics, or metolazone within a year prior to index date.Be aged ≥18 years on index date.Have at least two additional statin prescriptions 1 year following index date.Have at least one documented follow-up lipid test for TC, HDL-C, and LDL-C in the year prior to the start of follow-up.

Participants who die or experience MACE before the start of follow-up will be excluded. Each participant who meets the study eligibility criteria will be entered once for analysis; duplicate entries will be removed.

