### Outcomes and follow-up

The primary outcome of interest is MACE, defined as a diagnosis of either coronary heart disease, stroke, or cardiovascular death. Secondary outcomes include all-cause mortality and the individual components of the composite MACE outcome. Follow-up will begin after the end of the exposure assessment window (24 months after prescribing or dispensing of the first statin prescription) and will end at the earliest of outcome of interest, death, disenrollment or transfer from primary care practice, or end of the analysis period (31 December 2017).

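### Objective 1 compares MACE incidence between countries, but its only stated cohort is persistent, retested statin users who are event-free at 24 months

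*Protocol article*

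**What the plan says.** The protocol article gives objective 1 at the end of the Introduction: "To compare the incidence of MACE in adults taking statins for primary prevention of CVD between HK, NZ, and the UK". Objective 2 is the association between lipid levels at 24 months and MACE.

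Eligibility criteria opens with a rule for the whole study: "To be included in the study, each patient must meet the following eligibility criteria". Three of its conditions depend on what happens after the index date:

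- Early events, in the closing paragraph of that section: "Participants who die or experience MACE before the start of follow-up will be excluded"
- Repeat treatment: the patient must receive two or more further statin prescriptions during the first year of use.
- Retesting, the last item of the list: "Have at least one documented follow-up lipid test for TC, HDL-C, and LDL-C in the year prior to the start of follow-up"

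Outcomes and follow-up sets one start of follow-up, "24 months after prescribing or dispensing of the first statin prescription". Data cleaning and validation says that follow-up lipid values will not be imputed. Statistical analysis then plans crude rates per 1000 person years and names no other cohort or time origin for objective 1.

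**The concern.** The landmark suits objective 2: the exposure is a lipid level measured on treatment, so it must be known before events are counted. Objective 1 has no lipid exposure. It is a descriptive comparison of event rates, and the two reasons that Exposures gives for 24 months (when statin benefit appeared in trials, and capture of follow-up tests) do not bear on it.

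Applied to objective 1, the same cohort changes the population being described. Whether a patient is retested in the second year and keeps collecting prescriptions depends partly on how care is organised. Strengths and limitations expects the health systems to differ: hospital and specialist care leads in Hong Kong, primary care in New Zealand and the UK. If patients who are not retested have a different event rate, and the retested share varies by country, part of an observed rate difference could come from selection. The limitations mention differences between systems but not this route. Implications for research and practice says that the results will apply directly to policymakers in the three places.

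**Working it through.** **1. Which conditions each objective needs**

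| Condition | Needed for objective 2 | Needed for objective 1 |
|---|---|---|
| Lipid test in months 12–24 | Yes, it defines exposure | No |
| No death or MACE before month 24 | Yes, exposure precedes outcome | No |
| Follow-up from month 24 | Yes | No |
| Two further prescriptions | Design choice | Only if persistent use is meant |

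All four are applied to both objectives.

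**2. The plan's own event figure** (Feasibility assessment and sample size)

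Inputs: 140 000 Hong Kong patients after all criteria, 3 years, 10 MACE per 1000 person years.

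Events = 140 000 × 3 × 10/1000 = 4200. The stated figure is reproduced.

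**3. What the available figures can and cannot show**

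- Carrying the same rate back to the index date gives 140 000 × 2 × 10/1000 = 2800 events, and 2800/(2800 + 4200) = 40%. This does not measure bias. Under a constant rate, skipping 24 months removes events and person-time in proportion, and the rate is unchanged. The 140 000 are also, by definition, event-free at 24 months.
- 140 000/267 243 = 52% of the initial Hong Kong new users are kept. The 48% lost mixes pre-index criteria (heart failure, kidney disease, drug and baseline-test criteria) with post-index ones, and the article does not split it.

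**4. Depletion by early events** (assumed model)

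At 10 per 1000, the cumulative MACE hazard over 24 months is 0.02. Under gamma frailty with variance v, the rate at 24 months is multiplied by 1/(1 + 0.02v):

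- v = 1: 1/1.02, about 2% lower
- v = 3: 1/1.06, about 6% lower

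This part is small at the protocol's rate. Deaths from other causes would add an amount that the article does not give.

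**5. Selection by retesting** (assumed values)

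Let the rate among all users event-free at 24 months be 10 per 1000 in two countries, s the share retested, and k the rate in untested patients divided by that in tested patients. The tested-only rate is 10/(s + (1 − s)k).

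| k | s = 0.40 | s = 0.85 |
|---|---|---|
| 1.0 | 10.0 | 10.0 |
| 1.5 | 10/1.30 = 7.7 | 10/1.075 = 9.3 |
| 2.0 | 10/1.60 = 6.3 | 10/1.15 = 8.7 |

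Equal true rates can look different through testing coverage alone, and there is no distortion when k = 1. Neither s nor k is given for any site, so the table shows a mechanism, not an estimate.

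**6. Whether the sensitivity analyses help**

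Sensitivity analyses starts follow-up at day 91 or day 366, so some events before month 24 are counted there. Each analysis still assigns patients by a lipid test after statin start, and no incidence comparison in untested patients is described.

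**The case against.** The restriction is disclosed, so a careful reader can see whom the rates describe. A person-year rate does not suffer merely because early time is skipped, and depletion by early MACE looks small. The document gives no retesting share or event rate in untested patients, so no bias in the country comparison is demonstrated. Objective 1 also concerns people taking statins, which gives some reason to require repeat prescriptions. All of this stands as a limit on the size of the point. None of it makes the stated cohort the one that objective 1 names.

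Three stronger readings are tempting, and the document does not support them.

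- A reader might infer that the country ranking is distorted, or that 40% of events or 48% of patients measure the loss. Steps 3 to 5 of the working show why neither follows.
- A reader might infer that every event in the first two years is thrown away. The main analysis does not count them, but the sensitivity analyses count some.
- A reader might see a contradiction with Study design, which says "To prevent survival bias and covariate measurement bias, a new user, rather than a prevalent user, design will be used". That sentence contrasts new with prevalent users. With a fixed landmark everyone enters at the same time since initiation, so the contrast holds.

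Nor can condensation of a journal article explain the point: the criteria and the start of follow-up are stated for every patient.

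**Conclusion.** The point holds as a mismatch between objective 1 and the cohort that will answer it. As written, the rates are MACE incidence from month 24 in users with repeat prescriptions, a second-year lipid test and no earlier event. Selection may differ between the three health systems, and the planned sensitivity analyses do not remove it.

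No size or direction can be given. An effect on the comparison requires that patients left out have a different event rate from those kept, and that the selection differs by country. Both are plausible from the protocol's account of the health systems; neither is shown. The change is worth making because it is cheap and the comparison is a stated objective. Objective 2 is not affected.

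**What to change.** For objective 1, estimate incidence from the index date in all new users who meet the pre-index criteria. Do not apply the follow-up lipid test or the exclusion for early death or MACE, and do not condition on later prescriptions. If persistent use is intended, start person-time when the prescription condition is met, so that no event-free time is guaranteed.

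Report the 24-month landmark rate beside it, labelled as incidence from month 24 in retested, event-free users with repeat prescriptions. Give the numbers excluded by reason and by country. Leave the landmark cohort for objective 2 as it is.

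Cost: a second cohort definition to report and one extra incidence run per site. Each site must hold early events and deaths anyway in order to apply the exclusion. Access to the New Zealand data was still pending at submission, so it cannot be assumed that the data are in hand there. Selection through the compulsory baseline lipid test would remain and should be named as a limitation. If the second estimate is not run, objective 1 should at least be reworded to match the landmark cohort.

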**Method:**

New statin users without a history of atherosclerotic CVD, heart failure, or chronic kidney disease, with baseline and follow-up lipid levels will be eligible for inclusion. Patients will be classified according to LDL-C (<1.4, 1.4–1.7, 1.8–2.5, and ≥2.6 mmol/l) and non-HDL-C (<2.2, 2.2–2.5, 2.6–3.3, and ≥3.4 mmol/l) concentrations 24 months after initiating statin therapy. The primary outcome of interest is MACE, defined as the first occurrence of coronary heart disease, stroke, or cardiovascular death. Secondary outcomes include all-cause mortality and the individual components of MACE. Sensitivity analyses will be conducted using lipid levels at 3 and 12 months after starting statin therapy.

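### Most of the primary-prevention exclusions stop at the first statin, but exposure and follow-up start 24 months later, so new heart failure, CKD, PAD or TIA in between does not exclude

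*Protocol article*

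**What the plan says.** All references are to the protocol article.

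- **Index date** (Study design): "The cohort entry date (index date) is defined as the first dispensing or prescribing of a statin between 1 January 2007 and 31 December 2012".
- **Disease exclusions** (Eligibility criteria): coronary heart disease and "cerebrovascular disease (stroke or transient ischaemic attack), or peripheral artery disease (PAD), prior to index date". Heart failure, CKD and diabetes with CKD are added "due to their equivalent level of risk as people with established CVD, prior to index date".
- **Marker-drug exclusions** (same section): nitrates, other antianginals, peripheral vasodilators, "loop diuretics, or metolazone within a year prior to index date".
- **Between index date and follow-up** (same section): "Participants who die or experience MACE before the start of follow-up will be excluded".
- **Primary outcome** (Outcomes and follow-up): "The primary outcome of interest is MACE, defined as a diagnosis of either coronary heart disease, stroke, or cardiovascular death".
- **Time zero** (same section): "Follow-up will begin after the end of the exposure assessment window (24 months after prescribing or dispensing of the first statin prescription".
- **Population** (Abstract, Method): "New statin users without a history of atherosclerotic CVD, heart failure, or chronic kidney disease".

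The Covariates section names neither heart failure, CKD, PAD nor TIA among the required confounders or the additional ones.

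**The concern.** Fixing eligibility at the index date is normal when exposure and time zero are also there. Here both sit at a 24-month landmark. The protocol accepts this for MACE, which it removes up to the landmark, but it does not carry the rest of its own exclusion list forward.

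A diagnosis made in the gap can precede the lipid test. The qualifying test must fall in the year before follow-up, so in the primary analysis any diagnosis in months 0 to 12 comes before it, and a later one may. If the diagnosis changes lipid treatment or adherence, and also raises MACE risk, it is a confounder that the listed covariates do not capture directly.

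This bears on a stated question of the study. The Introduction asks whether there is a lipid level below which no further benefit is gained, and the section on implications would read an absent association at very low levels as grounds for less concern about missed targets. Bias toward the null in the lowest groups would resemble that finding.

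**Working it through.** **1. The plan's own figure.** Feasibility assessment and sample size gives about 140 000 Hong Kong (CDARS) patients, at least 3 years of follow-up and 10 MACE per 1000 person-years: 140 000 × 3 × 10/1000 = 4200 events. This reproduces the stated figure. The concern does not depend on it; it serves only to cost the fix.

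**2. Eligibility logic.**

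| Condition | Excludes before index date | Excludes in months 0–24 |
|---|---|---|
| Coronary heart disease | yes | yes, through MACE |
| Stroke | yes | yes, through MACE |
| TIA | yes, named separately from stroke | not as worded |
| PAD | yes | no |
| Heart failure | yes | no |
| CKD | yes | no |
| Marker drugs | yes (prior year) | no, unless a MACE diagnosis accompanies them |

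**3. How many patients.** The documents give no incidence for these conditions. Assume a combined 5 to 40 per 1000 person-years over 2 years. Share carried in = 1 − exp(−2 × rate):
- 5 per 1000: 1 − exp(−0.01) = 1.0%, about 1400 of 140 000.
- 40 per 1000: 1 − exp(−0.08) = 7.7%, about 10 800 of 140 000.

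**4. Possible bias.** Let pL and pH be the share of such patients in a low-LDL-C group and in the high group, and RR their relative MACE rate. Bias factor = (1 + pL(RR − 1)) / (1 + pH(RR − 1)), applied to the planned hazard ratio of 0.85. All three inputs are assumed.

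| pL | pH | RR | Factor | 0.85 appears as |
|---|---|---|---|---|
| 0.06 | 0.03 | 2 | 1.06/1.03 = 1.029 | 0.87 |
| 0.08 | 0.03 | 2.5 | 1.12/1.045 = 1.072 | 0.91 |
| 0.10 | 0.04 | 3 | 1.20/1.08 = 1.111 | 0.94 |
| equal | equal | any | 1.000 | 0.85 |
| 0.03 | 0.06 | 2 | 1.03/1.06 = 0.972 | 0.83 |
| 0.04 | 0.10 | 3 | 1.08/1.20 = 0.900 | 0.77 |

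Other pairings move the ends: (0.06, 0.04, RR 2) gives 1.06/1.04 = 1.019, or 0.87; (0.10, 0.03, RR 3) gives 1.20/1.06 = 1.132, or 0.96. A wider set, up to (0.15, 0.05, RR 3), gives 1.30/1.10 = 1.182, or 1.00. The first three rows are examples, not bounds.

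**5. Cost of excluding at the landmark.** With carried-in share p and relative rate k, the share of events lost is pk/(pk + 1 − p). For p = 1.0%, k = 1, 4158 of the 4200 events remain; for p = 7.7%, k = 3, 3360 remain. Power (Schoenfeld) = Φ(√(d·a·(1 − a)) × |ln 0.85| − 1.96), with d events and a the share of patients in the smaller group:
- a = 0.5: above 0.99 throughout.
- a = 0.1: 0.88 with all 4200 events, and 0.88 to 0.81 after exclusion.

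The plan's power statement refers to all three cohorts pooled, so these CDARS-only figures are conservative.

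**The case against.** **Primary prevention can be defined at initiation.** The second objective speaks of adults taking statins for primary prevention, and an indication can be fixed at the first prescription. That is a coherent population and it stands as an alternative. But the protocol neither says that later disease is deliberately kept in nor adjusts for it, and removing MACE up to the landmark points the other way.

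**The cohort remains largely as intended.** A reader might infer that it is no longer primary prevention at time zero. That is too strong: under the assumptions above, at least 92% of patients are unaffected.

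**The direction is open.** A reader might infer that low LDL-C will look falsely unhelpful. That needs new disease to be followed by intensified lipid lowering before the test. If it clusters with poor adherence and high LDL-C, the bias reverses. The documents do not settle which.

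**Part of the list is already covered.** Eligibility criteria counts angina and ischaemic heart disease as coronary heart disease. If MACE uses the same definition, most new antianginal users are already removed. A code list might also class TIA under stroke. Neither point covers heart failure, CKD or PAD.

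**Partial mitigation exists.** The covariates include antiplatelets, anticoagulants and antihypertensives (among them diuretics), which are partial proxies if measured near the landmark. The 3- and 12-month sensitivity analyses shorten the gap, and a drift of the hazard ratio across landmarks could be a signal. They do not close the gap.

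**Unseen material.** Figure 1 also shows inclusion and exclusion criteria and is not available here. The written criteria are nonetheless explicit.

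**Conclusion.** The gap in the text is real. Patients with new heart failure, CKD, PAD or TIA (unless coded as stroke) in the 24 months before follow-up are kept as primary prevention, against the protocol's stated population and its own reasoning about equivalent risk, and these diagnoses are not on its confounder list.

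The size and direction of any bias cannot be derived from the documents. The 1.0% to 7.7% carried in, and 0.85 appearing as 0.87 to 0.94, rest wholly on assumed incidence, prevalence by LDL-C group and rate ratios. Equal prevalence gives no bias from this source, and reversed prevalence gives an apparent hazard ratio below 0.85. The documents therefore do not support a claim that the study will show a false threshold. They support only that the design leaves this explanation open when it could be closed cheaply. Should-fix.

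**What to change.** **Preferred.** In Eligibility criteria, apply the listed exclusion diagnoses and drugs up to the start of follow-up of each analysis: 24 months for the primary analysis, and 3 and 12 months for the sensitivity analyses. All the information is available at time zero.

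**Alternative.** State that the population is primary prevention at statin initiation, adjust for heart failure, CKD, PAD and TIA recorded before the lipid test, and report a sensitivity analysis that excludes these patients at the landmark.

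In either case, state whether TIA counts as stroke within MACE, and whether the coronary heart disease component uses the definition in Eligibility criteria.

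**Cost.** One sentence in the common protocol and a changed look-back end date at each site, using data already held. Probably a few percent fewer patients, with little loss of power in the scenarios above. One drawback should be acknowledged: because the lipid test can be up to a year before follow-up, some excluded diagnoses will post-date it and could partly result from the lipid level. The existing MACE exclusion already has this feature. The alternative's adjustment avoids it by using only diagnoses made before the test.

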### Exposures

Serum concentrations of LDL-C and non-HDL-C 24 months after initiating a statin are the primary exposures of interest (Figure 1). The latest lipid test measurement for patients with multiple records for lipid tests during the exposure assessment window will be selected. If non-HDL-C has not been reported, it will be calculated as TC − HDL-C.^6^ This timeframe after statin initiation was selected as this is when a measurable benefit in reducing cardiovascular events from statin treatment occurred in randomised controlled trials.^22,23^ Furthermore, the 24-month time point ensures most follow-up cholesterol measures are captured in the electronic health records within each database.^12^

Patients will be categorised into four exposure groups according to lipid concentrations based on specific treatment targets recommended in clinical practice guidelines.^6,24^

For LDL-C:

<1.4 mmol/l (<55 mg/dl)≥1.4 to <1.8 mmol/l (≥55 to <70 mg/dl)≥1.8 to <2.6 mmol/l (≥70 to <100 mg/dl)≥2.6 mmol/l (≥100 mg/dl).

For non-HDL-C:

<2.2 mmol/l (<85 mg/dl)≥2.2 to <2.6 mmol/l (≥85 to <100 mg/dl)≥2.6 to <3.4 mmol/l (≥100 to <130 mg/dl)≥3.4 mmol/l (≥130 mg/dl).

### Outcomes and follow-up

The primary outcome of interest is MACE, defined as a diagnosis of either coronary heart disease, stroke, or cardiovascular death. Secondary outcomes include all-cause mortality and the individual components of the composite MACE outcome. Follow-up will begin after the end of the exposure assessment window (24 months after prescribing or dispensing of the first statin prescription) and will end at the earliest of outcome of interest, death, disenrollment or transfer from primary care practice, or end of the analysis period (31 December 2017).

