## Introduction

CVD is the leading cause of death globally.^1^ Atherogenic lipoproteins (LDL-C and non-HDL-C) are well-established risk factors for atherosclerotic CVD.^2,3^ Recent evidence from secondary prevention trials indicates that individuals with lower LDL-C concentrations have a reduced risk of subsequent cardiovascular events.^4,5^

While lower targets for LDL-C are gaining wider acceptance for secondary prevention of CVD, there remains limited evidence for specific lipid targets for primary prevention. The recent European clinical guidelines for the treatment of dyslipidaemia emphasise specific LDL-C and non-HDL-C targets for primary prevention according to level of CVD risk.^6^ However, whether achieving a specific lipid target while taking statin therapy for primary prevention corresponds to a reduction in cardiovascular events is uncertain, as most randomised controlled trials of statin therapy have not allocated patients to specific lipid targets. It is also unknown whether there is a lipid level threshold, below which no added clinical benefit is obtained, and if a 'lower is better' approach is appropriate for primary prevention of CVD. Understanding the lowest absolute beneficial level of LDL-C is important as very-low LDL-C levels are now achievable with proprotein convertase subtilisin-kexin type nine inhibitors, and emerging treatments such as inclisiran.^4,7^ The association between on-treatment cholesterol levels and risk of cardiovascular events has been assessed, but these have mostly been in secondary prevention statin trials, and whether these findings extend to clinical practice marked by individual variability in statin response requires further investigation.^8^

Ethnic group, and consequently pharmacogenomics, influences response to statin therapy, particularly for Asians.^9^ Variability in statin response may be present for other non-Caucasian ethnic groups. Moreover, organisation of health systems,^10^ statin dosing,^11^ and individual response to treatment^12^ vary and may impact the magnitude of benefit derived from statin therapy. Given these factors, an assessment of lipid levels in diverse populations is needed to provide representative data, as most primary prevention statin trials enrolled middle-aged Caucasians.^13^ Therefore, this study has two objectives:

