#### Subgroup analyses

To explore heterogeneity of exposure effect, subgroup analyses will be conducted by age, sex, LDL-C categories as in the FOURIER trial^4^ (that is <0.5 mmol/l, 0.5 to <1.3 mmol/l, 1.3 to <1.8 mmol/l, 1.8 to <2.6 mmol/l, and ≥2.6 mmol/l), statin adherence prior to follow-up, statin persistence, ethnic group, and prescribed statin dose intensity.

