### Strengths and limitations

The proposed study is significant; it includes a large number of patients from three different continents, allowing for comparisons between regions and ethnic groups. The estimates obtained from pooling the results will thus be both more precise and generalisable to the millions of patients globally who use statins for primary prevention of CVD. It will not assess the effects of very low concentrations of LDL-C such as haemorrhagic stroke and new-onset diabetes mellitus. In addition, heterogeneity between healthcare systems and electronic health records is anticipated, and will be considered in the interpretation of results. For example, public health care in HK is primarily driven by hospital and specialist care, whereas primary care providers in NZ and the UK act as the first point of contact and are gatekeepers to secondary care.

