### Implications for research and practice

The study will have implications for primary care clinicians, who often prescribe statins for primary prevention of CVD. Intensive monitoring of lipid response and prescribing of high-dose statins may not be practical or well adopted approaches for primary care clinicians. Not achieving guideline recommended targets may cause concern, but this concern may not be justified if very low lipid levels are not associated with a reduced risk of cardiovascular events in primary prevention of CVD. The results will generate important information about the potential benefits of achieving or not achieving current guideline recommended absolute cholesterol goals.

The evidence will also be of interest to guideline panels and policymakers, who make recommendations for the primary prevention of CVD. It will help further the understanding of the relationship of cholesterol and the future risk of CVD in three diverse international populations. By including patients from diverse ethnic groups from three regions, the results will be directly applicable to policymakers in the UK, NZ, and HK.

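### Stroke is counted without subtype, so a flat result at very low LDL-C could not be told apart from benefit offset by haemorrhagic stroke

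*Protocol article*

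**What the plan says.** All references are to the protocol article.

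- *Outcomes and follow-up*: MACE is "defined as a diagnosis of either coronary heart disease, stroke, or cardiovascular death". The Abstract (*Method*) has the same three components, "defined as the first occurrence of coronary heart disease, stroke, or cardiovascular death". Neither place limits stroke by type.
- *Outcomes and follow-up*, secondary outcomes: "Secondary outcomes include all-cause mortality and the individual components of the composite MACE outcome". Stroke is therefore reported once, undivided.
- *Strengths and limitations*: "It will not assess the effects of very low concentrations of LDL-C such as haemorrhagic stroke and new-onset diabetes mellitus".
- *Exposures* sets the lowest main LDL-C group at below 1.4 mmol/l. *Subgroup analyses* uses finer categories: "<0.5 mmol/l, 0.5 to <1.3 mmol/l, 1.3 to <1.8 mmol/l, 1.8 to <2.6 mmol/l, and ≥2.6 mmol/l".
- *Introduction*, on the motivation: "It is also unknown whether there is a lipid level threshold, below which no added clinical benefit is obtained".
- *Implications for research and practice*, on failing to reach targets: "this concern may not be justified if very low lipid levels are not associated with a reduced risk of cardiovascular events".

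No section excludes haemorrhagic stroke from the endpoint or plans an analysis restricted to ischaemic stroke.

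**The concern.** The protocol itself lists haemorrhagic stroke among the effects of very low LDL-C. If that effect exists, it runs opposite to the expected fall in coronary events and ischaemic stroke, and it does so in the groups where the study looks for a lower limit of benefit. Leaving a harm unstudied is harmless to the benefit estimate when the harm lies outside the endpoint. Here, on the plain reading, it lies inside.

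A hazard ratio near 1 in the lowest group then has two explanations that the planned outcomes cannot separate:

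1. atherosclerotic benefit has levelled off; or
2. atherosclerotic benefit continues and haemorrhagic stroke cancels part of it.

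These mean different things to the guideline panels the article addresses. If haemorrhagic stroke does not rise, that reassurance would not be visible either.

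**Working it through.** **The plan's own figure.** *Feasibility assessment and sample size* gives about 140 000 patients in the Hong Kong database (CDARS), at least 3 years of follow-up and 10 MACE per 1000 person years: 140 000 × 3 × 10/1000 = 4200 events, as stated. For HR 0.85, two-sided alpha 0.05 and power 0.80, the Schoenfeld formula with equal groups gives 4 × (1.960 + 0.842)² / (ln 0.85)² = 1189 events. Stroke type does not enter either calculation, so the sample size is not in error.

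**Dilution.** Let h be the share of reference-group events that are haemorrhagic, and HR_h the haemorrhagic hazard ratio in the lowest group. Then, approximately,

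combined HR = (1 − h) × 0.85 + h × HR_h.

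The 0.85 is the plan's HR, applied here by assumption to the non-haemorrhagic events. The values of h and HR_h are assumptions; the documents give none.

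| Outcome | h | HR_h | Combined HR |
|---|---|---|---|
| MACE | 2% | 1.0 | 0.98 × 0.85 + 0.02 × 1.0 = 0.853 |
| MACE | 5% | 1.5 | 0.95 × 0.85 + 0.05 × 1.5 = 0.8825 |
| MACE | 10% | 1.5 | 0.90 × 0.85 + 0.10 × 1.5 = 0.915 |
| Stroke | 10% | 1.0 | 0.90 × 0.85 + 0.10 × 1.0 = 0.865 |
| Stroke | 20% | 1.5 | 0.80 × 0.85 + 0.20 × 1.5 = 0.980 |
| Stroke | 30% | 1.5 | 0.70 × 0.85 + 0.30 × 1.5 = 1.045 |

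**Effect on information.** Across the MACE range of 0.853 to 0.915, the same formula requires 1242 to 3979 events with equal groups, against 1189. If 10% of patients are in the lowest group (assumption), power from the 4200 CDARS events alone is 88% at HR 0.85. It falls to 85% at h = 5% with HR_h = 1.0, and to 68% at h = 5% with HR_h = 1.5. These figures understate the planned study, which pools three databases.

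**The case against.** **No contradiction.** A reader might infer that the endpoint contains an event the protocol says it leaves out. The text does not support that. The limitations sentence removes nothing from MACE; it says there will be no dedicated look at this harm, and an all-stroke MACE fits it. This part of the objection stands.

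**All stroke is an inference.** The article shows no code lists, and *Data cleaning and validation* leaves operational definitions to a harmonised common protocol. This also stands, as a limit on certainty. It does not remove the point: if the codes are limited to ischaemic stroke, the outcome definition should say so; if not, the ambiguity described here applies.

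**Net effect is a legitimate target.** A haemorrhagic stroke is a cardiovascular event, and a null MACE result would be a fair answer to the question of net benefit. This is why the primary endpoint should stay as it is. It does not settle whether atherosclerotic benefit has a floor, and reporting stroke, coronary disease and mortality separately would show a divergence without showing its cause.

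**The size rests on outside assumptions.** This is correct. The plan's 0.85 was also set for MACE as a whole; assigning it to non-haemorrhagic events is a choice. A reader might go further and conclude that the composite could reverse or that the study is underpowered. Neither follows: in the range above the MACE HR stays below 1, and even 3979 events (equal groups) is fewer than CDARS alone expects.

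**Conclusion.** The point holds as a problem of interpretation in the lowest LDL-C groups. It is neither an internal contradiction nor a numerical error. As written, the plan cannot distinguish a plateau from an offset below 1.4 mmol/l, or below 0.5 mmol/l in the finer categories, and this bears on its threshold question and on its intended reading of a null result.

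The likely effect on MACE is modest (HR 0.853-0.915 in place of 0.85). The stroke component, a named secondary outcome, is more exposed (0.865-1.045): at the upper end a 15% reduction in other strokes would be hidden or reversed. Both ranges depend on the assumed haemorrhagic shares and hazard ratios, and on stroke meaning all stroke. A change is worth making because it is cheap, not because the primary analysis is invalid.

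**What to change.** 1. Keep the primary MACE as defined.
2. In *Outcomes and follow-up*, state which stroke types count, and split stroke by diagnosis code into ischaemic or unspecified and haemorrhagic, in the same way at all three sites.
3. Add a prespecified sensitivity analysis of MACE and of the stroke component that counts only ischaemic or unspecified stroke. State how fatal haemorrhagic strokes are handled, since they could otherwise re-enter through cardiovascular death.
4. Report haemorrhagic stroke separately across the same LDL-C and non-HDL-C groups.
5. Amend the haemorrhagic-stroke part of the sentence in *Strengths and limitations* to match. New-onset diabetes can remain there as a stated limit; nothing in this point calls for adding it as an outcome.

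**Cost.** One split of a code list and a few more model runs per site. Some strokes will be coded as unspecified, and haemorrhagic events in the lowest group will be few. For example, if 5% of the 4200 CDARS events are haemorrhagic (210) and 10% of those fall in the lowest group (both assumptions), there are 21 events there and 189 elsewhere. The standard error of the log HR is √(1/21 + 1/189) = 0.23, so the 95% interval runs from the estimate divided by about 1.57 to the estimate multiplied by about 1.57. That is wide, but it shows what the undivided component cannot.
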